## Abstract

**Background:**

Psychological distress, defined as depression, anxiety and perceived stress, during pregnancy is common, with 15–25% of women experiencing clinically significant levels of such distress. Despite the far-reaching impact of prenatal psychological distress on mothers and their children, and that women are receptive to screening, few providers routinely screen for prenatal psychological distress and less than one in five women will receive the mental health care that they require. There is a lack of certainty regarding the most effective treatments for prenatal psychological distress. No online interpersonal psychotherapy (IPT) trials have been conducted that focus on improving psychological distress in prenatal women. The purpose of this pilot randomized controlled trial is to evaluate the perspectives of pregnant women on the feasibility and acceptability of online IPT (e-IPT) delivered during pregnancy.

**Methods:**

A pilot randomized controlled trial design with repeated measures will evaluate the feasibility and acceptability of e-IPT for pregnant women compared to routine prenatal care. Qualitative interviews with 15–30 individuals in the intervention group will provide further data on the feasibility and acceptability of the intervention. Assessment of feasibility will include the ease of accessing and completing the intervention. Women will also be asked about what barriers there were to starting and completing the e-IPT. Assessment of acceptability will inquire about the perception of women regarding the intervention and its various features. A sample size of 160 consenting pregnant women aged 18 years and older will be enrolled and randomized into the experimental (e-IPT) or control (routine care) condition. The secondary outcome measures include: depression, anxiety and stress symptoms; self-efficacy; self-mastery; self-esteem; relationship quality (spouse, immediate family members); coping; and resilience. All participants will complete the aforementioned measures at baseline during pregnancy (T_1_), 3 months postrandomization (T_2_), at 8 months of pregnancy (T_3_), and 3 months postpartum (T_4_).

**Discussion:**

The results of this pilot randomized controlled trial will provide data on the feasibility and acceptability of the intervention and identify necessary adaptations. This study will allow for optimization of full trial processes and inform the evaluation strategy, including sample size calculations for the full randomized controlled trial.

**Trial registration:**

ClinicalTrials.gov, NCT01901796. Registered on 18 December 2014.

## Background

### Prenatal psychological distress

The perinatal period is a time of increased vulnerability where women experience greater probability of psychological distress [1, 2]. Psychological distress during pregnancy is common, with 15–25% of women experiencing clinically significant levels of depression, anxiety and stress [3]. While affective disorders have frequently been attributed to hormonal changes [4], the greatest risk factors include modifiable lifestyle factors, including the partner relationship and social support [5]. Left untreated, prenatal psychological distress is associated with poor obstetrical outcomes and maternal functioning, increased incidence of poor child development and cognitive delays, interpersonal conflict, parenting stress, and maternal postpartum mood disorders [6–9].

### Under-detection and under-treatment of prenatal psychological distress

Prenatal maternal psychological distress has a significant and far reaching impact on mothers and their children [6]. There are well-established recommendations for routine mental health screening during the perinatal period [10]. Unfortunately, less than one in five providers routinely screen for perinatal mental health concerns [11]. Equally concerning is that only one in seven perinatal women will receive the mental health intervention they need [11, 12].

There is a lack of certainty regarding the most effective treatments for prenatal psychological distress. The US Preventive Services Task Force completed a systematic evidence review on interventions to prevent perinatal depression [13]. Of the 20 counseling intervention studies included, most using cognitive behavioral therapy (CBT) or interpersonal psychotherapy (IPT), half delivered the intervention to pregnant women and half to postpartum women in the USA [13]. Across these interventions, absolute reductions in risk of depression ranged from 1.3% greater reduction in the control group to 31.8% in the intervention group [13]. No harms, potential or actual, of the interventions were reported. Acceptability of the intervention was reported as positive in several of the studies (*n* = 6) and participants felt that the interventions were beneficial and enjoyable [13]. This review indicated that interventions are effective when delivered during pregnancy, the postpartum period, or both.

These US Preventive Services Task Force findings are similar to another recent literature review that endorsed the moderate treatment effect and lasting benefits of CBT and IPT for pregnant women with a major depressive disorder [14]. Both systematic literature reviews and the US Preventive Services Task Force recommendation statement call for future research on treatments for all mental disorders during pregnancy and larger scale effectiveness trials of CBT and IPT [13–15]. Additionally, significant health system-level limitations in accessing therapies should be addressed [15–17]. In addition to a lack of perinatal-specific training/resources (differentiating between prenatal and postpartum intervention), and non-baby-friendly environments, in-person providers cannot meet the needs of women during the perinatal period [17].

### Interpersonal psychotherapy: aim and effectiveness

The aim of IPT is to improve social support networks since enhanced social support predicts greater psychological adjustment to stressors; IPT is therefore a promising intervention for prenatal women [18–21]. IPT is a short-term dynamic attachment-based psychotherapy [22, 23] aimed at symptom reduction and improved interpersonal relationships through enhanced social support [23]. The primary foci of treatment with IPT are the interpersonal issues of grief and loss, interpersonal disputes, and role transitions (Stuart, 2012). IPT attempts to provide clarification of individuals’ feelings, expectations, interactions, social roles, education, and social competence [24]. Additionally, IPT practitioners endeavor to assist individuals in establishing or better mobilizing support networks [23]. Individual functioning is believed to be based on a combination of intrapersonal factors (temperament, personality and attachment style) in relation to interpersonal factors (social support and quality of relationships) [23].

IPT is a highly effective treatment for depression and anxiety [25–30]. Randomized controlled trials of IPT in perinatal women found that IPT improved symptoms of depression and anxiety [20, 31–35] and functioning [9, 36]. The US Preventive Services Task Force showed convincing evidence that IPT is effective in preventing perinatal depression [13]. A 2011 meta-analysis found that IPT was more effective than CBT for treating perinatal depression [36]. A 2011 meta-analysis also found that IPT was more effective than couples therapy in the treatment of depressive symptoms during the perinatal period [37].

Automatic internet-based therapy interventions offer access to psychological resources at reduced costs, can be accessed from across the world, and can be accessed at any time. Research supporting the use of internet interventions for the prevention and treatment of perinatal mental health concerns is limited but several trials have demonstrated preliminary effectiveness in the prevention [38–40] and treatment of postpartum depression [41–43]. The recommendations from the gaps in the literature leads towards a trial of online IPT (e-IPT). To date, no trials have focused on improving psychological distress in prenatal women as a result of receiving e-IPT.

### Predictors and moderators of response to internet-based psychotherapy

CBT and IPT are reported to have similar effectiveness in reducing depressive symptoms [44–47]. Donker et al. concluded that, even when treatments are determined equally effective, there are individual characteristics (gender, age, education level, marital status, baseline depression level, coping skills, and previous depression) that influence treatment outcomes [28]. Individual characteristics that influence treatment effectiveness can be broken down into predictors and moderators [28]. Both predictors and moderators are considered pretreatment variables; however, the predictors forecast mental health outcomes in the intervention groups, while moderators identify persons more likely to benefit from particular treatments [28]. Examples of predictors of the efficacy of internet-based interventions include whether the internet-based therapies (CBT, IPT) are guided [28, 48], being female, obtaining low mastery scores on self-mastery measures and low dysfunctional attitudes on coping questionnaires [28]. A moderator of internet-based therapy is age, with evidence indicating that older adults benefit from CBT and younger adults demonstrate larger improvements with IPT [28]. A moderator of IPT is also a role transition, with role transitions occurring in younger adults of childbearing years [28]. Individuals undergoing role transitions are thought to benefit more from internet-based IPT because of the foci of IPT; specifically, interpersonal conflicts and role transitions are particularly relevant in their stage of life [28, 49]. As a result, it is expected that younger adults navigating a significant role transition (e.g., being pregnant and becoming a mother) would benefit from guided, internet-based IPT to improve symptoms of depression, anxiety, stress and interpersonal functioning [50].

### The challenge of IPT

IPT is an intervention endorsed as being effective for perinatal women with a history of depression and for individuals currently experiencing depressive symptoms [13]. IPT contains specific components such as developing a support system, effective communication, and skills to manage conflict in relationships for women during the perinatal period [13]. Despite IPT being an effective treatment for perinatal women, access to face-to-face IPT remains a challenge due to there being few trained IPT therapists, long wait times to access care, and high costs to access therapy [51, 52].

There is a need to make effective interventions more available and accessible for pregnant women. Online psychotherapy is an ideal treatment option for individuals as it overcomes major obstacles to psychological support including long wait times, lack of time, the stigma of accessing care, and financial burden [51]. In addition to higher levels of patient adherence and convincing reductions in mental health symptoms, online treatment options are readily available and cost-effective options to face-to-fact treatment [52]. Additionally, online psychological treatments are more effective and significantly less expensive than face-to-face therapy, are stable in the short and long term, and adherence rates are 80% [53]. In a meta-analysis of online psychotherapy, the advantages of online therapy included convenience, ability for individuals to proceed at their own pace, low cost, no wait times, high effect size, and superior attendance compared to face-to-face or group therapy [52]. Our study addresses the challenge of face-to-face IPT by evaluating online delivery of IPT.

### Research objectives, questions, and hypotheses

The primary aim of this pilot randomized controlled trial is to examine feasibility and acceptibility of e-IPT for prenatal women. The assessment of feasibility will include the percentage of women in the intervention group who report that the e-IPT is integrated as a component of prenatal care without difficulty. Acceptability will be assessed in terms of the percentage of women in the intervention group who report that modules and activities in e-IPT are easily understood and navigated. The primary research objective, question, and hypothesis are described in Table 1. The secondary objectives include assessment of symptoms of anxiety, depression, overall psychological distress, relationship quality (spouse, immediate family members), and mother resilience compared to routine care. We hypothesize that the e-IPT intervention will reduce symptoms of distress, anxiety and depression and will be significanly more effective compared to usual care. These secondary research objectives, questions, and hypotheses are described in Table 2.

**Table 1 Tab1:** Primary objective, research questions, and hypothesis

	Objective	Research questions	Testable hypothesis
1	To assess the feasibility and acceptability of online interpersonal psychotherapy for prenatal women	Do prenatal women find the online IPT intervention is easily integrated as a component of prenatal care without difficulty? Do prenatal women find the online IPT intervention acceptable? What will improve the performance of online interpersonal psychotherapy in a full trial version for prenatal women? Is it feasible to enroll and retain prenatal women in a study to assess an online IPT intervention? Is it feasible to perform data collection procedures as planned? Is it feasible to deliver the IPT program as intended?	Prenatal women will define strategies to enhance online interpersonal psychotherapy, readying it for a full trial

*IPT* interpersonal psychotherapy

**Table 2 Tab2:** Secondary objectives, research questions, and hypotheses

	Objective	Research question	Testable hypotheses
1	To evaluate the clinical effectiveness of online interpersonal psychotherapy versus routine care on reducing stress, anxiety, and depression in prenatal women	What is the effect of an online interpersonal psychotherapy intervention compared to routine care on the percentage of prenatal women with symptoms of stress, anxiety, and depression?	The percentage of prenatal women with stress, anxiety and depression about the clinical cut-offs of validated tools will be significantly lower in the intervention group versus routine care
2	To evaluate the effectiveness of the online interpersonal psychotherapy intervention compared to routine prenatal care on relationship distress	Is relationship distress reduced in the online interpersonal psychotherapy intervention group compared to the routine prenatal care control group?	Relationship distress will be significantly reduced in the online interpersonal psychotherapy group
3	To identify factors, mediators and moderators that are associated with effectiveness of the intervention among participants within the intervention group	What factors, mediators, and moderators are associated with the intervention effect?	Among participants in the intervention group, no factors will be significantly associated with the intervention effect, indicating that online interpersonal psychotherapy is appropriate for prenatal women

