### Definition and measurement of outcomes

#### Primary outcomes

The primary outcome of this pilot study is the feasibility and acceptability of e-IPT for pregnant women. Feasibility of the e-IPT intervention will also include an examination of enrollment and retention of women in the study. Additionally, the assessment of feasibility will assess adherence to the planned methods of data collection and intervention delivery. The feasibility interviews with 30 participants in the intervention group will ask women to comment on how easy it was to access and complete the intervention, as well as how long it took to complete the modules. In this study we also define feasibility as the percentage of women in the intervention group who report that the e-IPT intervention is easily done as a component of care during the perinatal period. Women in the e-IPT intervention group will also answer questions rating their experiences of the intervention. Women in the intervention group will answer questions to assess their views of e-IPT (for example, ‘were you comfortable using e-IPT with an online coach for therapy?’). Women in the intervention group will also be asked about suggestions for improving the e-IPT.

In this study we define acceptability as the percentage of participants in the intervention group who report that e-IPT is acceptable, the percentage of participants reporting that the e-IPT modules were easy to understand and navigate, the percentage of participants who found that the information in the module was effective in achieving intended outcomes, and whether the exercise was clear and easy to understand. Additionally, participants in the intervention group will be asked whether they would recommend the module to a pregnant friend. Women receiving the e-IPT will also be asked several questions to evaluate their user experience with the modules.

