#### Secondary outcomes

##### Psychological outcomes

Secondary outcomes of this pilot study evaluate the effectiveness of e-IPT compared to routine prenatal care with respect to a variety of intraindividual and interpersonal outcomes (Table 2), specifically stress, anxiety, depression, and relationship quality in prenatal women. The DASS21 is a 21-item questionnaire used to examine three self-report subscales including depression, anxiety, and stress over the previous week. Responses are recorded on a Likert-type scale ranging from 0 (not applicable at all) to 3 (applicable very much of the time) [56]. Based on the scores of each domain (raw scores multiplied by 2) the severity is graded into normal, mild, moderate, severe, or extremely severe [56]. The DASS21 is a well-validated (concurrent validity coefficients were 0.87 and 0.84) and reliable (test–retest and split-half reliability coefficient scores of 0.99 and 0.96) questionnaire [57] that has been previously used in perinatal samples [58–61]. The EPDS will be used to assess symptoms of depression experienced during pregnancy and the postpartum period. The EPDS is a well-validated questionnaire that has been previously used in pregnant women [62–65]. The EPDS is a 10-item self-report questionnaire used to assess perinatal depression (eight items) and anxiety (two items) over the previous week [66]. The questions are a Likert scale scored from 0 to 3 (with every changing anchors) with higher scores indicating more depressive symptoms. The EPDS is well validated, with sensitivity and specificity of 86% and 78%, respectively [67]. There is also good reliability for the EPDS, with test–retest reliability of 0.92 [68]. Additional secondary outcomes will be evaluated including relationship quality, resiliency, maternal–infant attachment, infant behavior, and parenting stress/competence.

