### Sample size estimation

The DASS21 categorizes women as having normal, mild, moderate, severe, and extremely severe depression, anxiety and stress [56]. To shift women from ‘midrange’ moderate symptoms down to mild severity on the depression, anxiety and stress subscales, these women would require a reduction of four points in each subscale. Based on the sample size formula for comparison of two means (two-tailed) at a significance level of 5% (1.96), a power of 80% (0.84), and a minimally clinically important difference of four points, 204 women with mild to moderate psychological distress are required in the trial. Based on a 25% prevalence rate of low–moderate prenatal psychological distress [69–71], a final sample size of 816 eligible women (408 per group) would be needed. This corresponds to a moderate effect size (*d* = 0.50) for depression, which is consistent with a meta-analysis of effect sizes of e-IPT [25]. Therefore, this final sample size of 816 participants is adequate to address the primary and secondary research questions of a full trial. Accounting for a participation rate of 50% based on previous studies of psychotherapy in pregnant women [55, 72, 73], the exclusion of 15% of women who do not meet study criteria (5% high psychosocial risk [70, 71, 74], 10% non-English speaking women), an attrition rate of 25% based on previous studies of perinatal IPT [20, 55], and a 5% loss to follow-up, 1592 women would need to be invited to participate in the study to achieve the final full trial sample size. As this is a pilot study, obtaining a sample size of 10% of the full trial sample is sufficient [75]; therefore 160 participants will be included in the pilot study with 80 participants in the intervention and control groups, respectively.

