#### Quantitative analysis

The quantitative dataset will be analyzed using IBM SPSS Statistics software. Missing values will be managed by using multiple imputation [78]. Assessment of the presence of any outliers will be made, and it will be determined if they are true values or data entry errors [78]. If not determined as an entry error, the analysis will be run with the outliers included and then run without the outliers included. Results will be compared and whether the outliers skew the results and what it means on a clinical level will be reported. If the results do not differ, then the analysis with the outliers included will be used. Outcomes will be assessed based on the number of modules completed. Additionally, a sensitivity analysis will be completed by running a negative binomial regression model which accounts for variance in the data. Descriptive statistics (mean/standard deviation or frequency/proportions) will serve to describe the characteristics of participants and assess group equivalence at baseline. Repeated measures analysis of variance will be used to determine the effectiveness of the intervention. The variables will be included in the analysis as covariates and bivariate analysis will be performed first. Those variables found to be statistically significant at the bivariate level will be included in the multivariate model. Analysis will adhere to the intent-to-treat principle [78].

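### The pilot's secondary effectiveness hypotheses are worded as confirmatory tests, although its stated purpose is feasibility and the effectiveness sample size belongs to the full trial

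*Protocol article*

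**What the plan says.** The Primary outcomes section is clear about what the pilot is for: "The primary outcome of this pilot study is the feasibility and acceptability of e-IPT for pregnant women". The Data analyses section handles that outcome with descriptive statistics and thematic analysis. The Discussion paragraph of the abstract gives the same purpose: feasibility, acceptability, necessary adaptations, and input to the full trial, including its sample size.

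The effectiveness outcomes are ranked secondary but are phrased as tests to be passed:

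- Research objectives, questions, and hypotheses: "We hypothesize that the e-IPT intervention will reduce symptoms of distress, anxiety and depression and will be significanly more effective compared to usual care".
- Table 2, secondary objective 1: the percentage of women with stress, anxiety and depression, judged by clinical cut-offs, "will be significantly lower in the intervention group versus routine care".
- Table 2, secondary objective 2: "Relationship distress will be significantly reduced in the online interpersonal psychotherapy group".
- Psychological outcomes: "Secondary outcomes of this pilot study evaluate the effectiveness of e-IPT compared to routine prenatal care". Depression is measured on both the DASS21 and the EPDS. The list then grows: "Additional secondary outcomes will be evaluated including relationship quality, resiliency, maternal–infant attachment, infant behavior, and parenting stress/competence".
- Quantitative analysis: "Repeated measures analysis of variance will be used to determine the effectiveness of the intervention".

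The Sample size estimation section gives the only significance level (two-tailed 5%) and the only power (80%). Both belong to the calculation that leads to 816 women, a number it calls adequate for the research questions of a full trial. The pilot has 160 women, 80 per group.

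**The concern.** The primary outcome is descriptive, so the hypotheses of a significant difference between arms are all about effectiveness. They cover at least four constructs (stress, anxiety, depression, relationship distress), or five scales once the EPDS is counted beside the three DASS21 subscales. The article does not say which of them decides, and it does not say that they are exploratory.

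This wording goes beyond the pilot's own stated purpose and sizing. If it is followed, one scale reaching p<0.05 can be reported as confirming a hypothesis stated in advance, whatever the others show. The DASS21 depression subscale and the EPDS could also disagree, with nothing to say which answers the depression hypothesis. In the other direction, a non-significant result could be read as failure of the hypothesis in a study that was not sized to test it.

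**Working it through.** **1. The plan's own figures.** The document gives no overall false-positive rate for the pilot, so there is none to reproduce. The sample size figures show only which study the tests belong to.

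- 204 / 0.25 = 816, as stated, for the full trial.
- 204 itself does not follow from d = 0.50 alone: 2 × (1.96 + 0.84)² / 0.50² = 62.7, so 63 per group and 126 in total.
- 160 is about 10% of the 1592 women to be invited (159.2), not of the 816 to be enrolled (81.6).

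The last two mismatches do not affect this point. What matters is that the section attaches the effectiveness sample size to the full trial and derives the pilot size as a fraction, with no power statement for the pilot.

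**2. Purpose against hypotheses.** The abstract's Discussion and the Primary outcomes section limit the pilot to feasibility, acceptability and informing a full trial. Research objectives, Table 2 and Quantitative analysis predict significance and use ANOVA to settle effectiveness. No sentence reconciles the two.

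**3. Size of the problem.** Inputs:

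- Number of tests k: 4 (constructs in Table 2) or 5 (three DASS21 subscales, EPDS, relationship distress).
- Two-sided 5% per test. This is an assumption, because the document states 5% only for the full-trial calculation.
- One test per measure, no true effect.
- Equal correlation ρ between test statistics. This is an assumption, varied from 0.3 to 0.8.

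For normal test statistics with common correlation ρ, the chance of at least one result with |z| > 1.96 is

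1 − ∫ φ(u) [Φ((1.96 − √ρ·u)/√(1−ρ)) − Φ((−1.96 − √ρ·u)/√(1−ρ))]^k du.

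Counting only results that favour e-IPT, it is

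1 − ∫ φ(u) [Φ((1.96 − √ρ·u)/√(1−ρ))]^k du.

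With ρ = 0 and k = 4 these reduce to 1 − 0.95⁴ = 18.5% and 1 − 0.975⁴ = 9.6%.

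| Tests | ρ | Either direction | Favouring e-IPT only |
|---|---|---|---|
| 4 | 0.3 | 17.4% | 8.7% |
| 4 | 0.5 | 15.6% | 7.8% |
| 4 | 0.8 | 11.4% | 5.7% |
| 5 | 0.3 | 20.9% | 10.5% |
| 5 | 0.5 | 18.3% | 9.1% |
| 5 | 0.8 | 12.7% | 6.4% |
| 1 | – | 5% | 2.5% |

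The further secondary outcomes (resiliency, attachment, infant behaviour and so on) are left out because no significance hypothesis is stated for them.

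**The case against.** The strongest reply is that this is a condensed article about a pilot. The protocol hypothesises superiority and does not assert it. The outcomes are ranked secondary, and the full trial is kept apart from the pilot in the sample size section. No passage makes progression to the full trial depend on a significant effectiveness result. A testing hierarchy, a split of alpha or a named contrast for secondary outcomes could well sit in a statistical analysis plan that is not shown.

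Much of this stands. The absence of a multiplicity rule is not a finding here, and it would be wrong to say that the pilot already declares e-IPT superior. But ranking an outcome as secondary does not make its test exploratory, and an analysis plan held elsewhere would not remove the significance wording in the published objectives, Table 2 and the analysis section.

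Stronger readings are also tempting, and the documents do not support them:

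- A reader might multiply the measures by the three post-baseline visits and infer a false-positive chance of a third or more. With four constructs at three visits, simulation gives 35.7% at correlations of 0.5 between outcomes and over time, and 26.6% at 0.7 for both. That needs a separate test at each visit. Quantitative analysis names repeated measures ANOVA and plans no such tests.
- A reader might infer very low power, because only a quarter of the pilot (about 20 women per group) would be distressed. The article states no analysis restricted to those women.
- A reader might take the phrase "these women would require a reduction of four points in each subscale" to mean that all three subscales must succeed together, so that joint power falls below 80%. No passage sets that rule, and the calculation concerns the full trial.

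**Conclusion.** The point holds as one of wording that changes what the pilot may conclude. The secondary hypotheses are confirmatory in form, cover several measures without a deciding one, and sit in a study whose stated purpose and sample size do not support confirmatory conclusions on effectiveness.

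In size, a wholly ineffective programme would give at least one significant result with a chance of about 11–17% (four constructs) or 13–21% (five scales), against 5% for a single test. A false result in favour of e-IPT has a chance of about 6–10.5% against 2.5%, roughly two to four times nominal. These figures rest on the assumed 5% level, one test per measure and equal correlations of 0.3 to 0.8. They would be higher only if visits were tested separately.

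**What to change.** Three places need rewording:

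- **Research objectives, questions, and hypotheses:** label the between-arm effectiveness comparisons in the pilot as exploratory, and replace the prediction of significantly greater effectiveness with the aim of estimating the between-arm difference and its 95% confidence interval.
- **Table 2, objectives 1 and 2:** replace the two significance hypotheses in the same way.
- **Quantitative analysis:** say that the ANOVA serves to estimate between-arm differences, reported with 95% confidence intervals, and that no conclusion on effectiveness will be drawn from the pilot.

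This costs text only; no data, visits or participants are added. The real price is that the pilot can no longer report a significant effect of e-IPT. The estimates and their intervals remain available for planning the full trial, which is the use the abstract gives them.
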